### Flow mediated dilation

Brachial artery FMD in response to hyperemia will be performed using an ultrasound device (Toshiba model Nemio XG, Japan) as an indirect measurement of endothelial function, adapted to the current guidelines.^
35
^

### Hydration protocol

On the day prior to heat exposure, participants will be instructed to drink 12 mL/kg^-1^ of water (in addition to usual liquid consumption). During the morning of the experimental session, the participants will be instructed to consume 6 mL/kg^-1^ of water, in addition to the usual liquid consumption, to ensure a state of euhydration. Prior to entering the environmental chamber, a urine collection will be performed to verify the state of hydration, using the specific gravity measured through a refractometer^
36,37
^ and assessment of the urine color through the Armstrong urine color chart.^
38
^ A urine specific gravity cutoff of 1.25 will be applied. For higher values, the participants will drink 200–250 mL of water and wait 30 min before heat exposure to ensure that they are normally hydrated before the session.

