^ Participants will be housed in an environmental chamber initially set at 55.0°C on three non-consecutive days of the week. Each session will last 60 min. During the sessions, the rectal temperature, heart rate (HR), blood pressure, and heat discomfort will be constantly measured. According to pilot testing, this protocol induces an approximate 1.2°C raise in the individual’s core temperature and remains increased after the session for an additional 15 min, before it starts to drop (Figure 1a). The HR increases and blood pressure, particularly diastolic pressure, decreases during the session (Figure 1b and Figure 1c, respectively). The core temperature initially decreases (10-15 minutes after the beginning), probably owing to rapid skin vasodilation and a blood flow shift from the center to the periphery. After approximately 20 min in the chamber, the core temperature starts to rise, as expected. The characteristics of the participants from the preliminary study are shown in Table 2.

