### Body temperature assessment and thermal sensation

To measure the rectal temperature, a flexible thermometer (RET-1 Physitemp Instruments, Clifton, New Jersey, United States of America) will be inserted 10-12 cm beyond the anal sphincter (self-inserted by the participant following the researcher’s instructions). Skin thermometers will measure the skin temperature on the upper back, arm, and leg (left hemibody) (SST1, Physitemp). The environmental chamber will be set at 55.0°C. Participants’ temperatures will be continuously monitored and recorded every 5 min throughout the session. If a participant reaches a rectal temperature > 39.0°C and presents symptoms such as nausea, disorientation, tiredness, abdominal pain, or headache, the session will be stopped. In addition to temperature measurements, a perceptual scale was used to identify thermal sensation and thermal comfort. To this end, participants will be asked about their thermal sensation (9-point scale from “very cold” to “very hot”) and thermal comfort (6-point scale from “very comfortable” to “very uncomfortable”) every 10 min during the session.^
23
^

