### Statistical considerations

To assess the effect of exercise on plasma HSP levels between the groups post-intervention, we assumed 80% power, 5% significance level, and an effect size (Cohen’s F) of 0.4. We estimated a dropout rate of 10%, and the calculated total number of patients was 22 in each group.^
24
^

The randomly assigned participants’ data will be analyzed according to the intention-to-treat principle as the primary choice and the per-protocol principle, with treatment, time, and treatment-time interaction registered as fixed effects. We will qualitatively document the reasons for, and details of, each withdrawal case. The normality of the data will be tested using the Shapiro-Wilk test. Mean and standard deviation will be used to describe parametric continuous variables, with median and interquartile range for non-parametric variables, and absolute and relative frequencies for categorical variables. Analysis of variance (ANOVA) will be used to compare the final outcomes. Treatment effects (group, time, and group interaction) will be estimated using Generalized Estimation Equations (GEE), followed by the Bonferroni post-hoc test (P < 0.05). Multiple linear regression analysis (backward method) will be performed to investigate the impact of routine pharmacotherapy, sex, and age on the primary and secondary outcomes. SPSS Professional software (version 20.0; IBM Corp., Armonk, New York, United States) will be used for all analyses.

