### Safety and adverse events

Participants will be under continuous health professional control for at least 30 min after the intervention to prevent adverse events. The following mild and moderate adverse events can occur. Exercise protocols, particularly during maximum effort, can cause discomfort (nausea and muscle soreness). Heat therapy has been shown to be safe for most people.^
17
^ However, for some participants, it is possible that the higher temperature caused thermal discomfort. Cardiovascular changes, such as increased heart rate and blood pressure, are expected and are not harmful. Mild dehydration may be observed after completion of the protocol and will be attenuated by proper hydration.

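### The urine specific gravity cutoff of 1.25 is above any attainable urine value, so the hydration check before heat exposure can never delay a session

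*Protocol article*

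**What the plan says.** The Hydration protocol section of the Protocol article instructs heat-arm participants to drink extra water the day before (12 mL per kg) and on the morning of a session (6 mL per kg). Before chamber entry, "a urine collection will be performed to verify the state of hydration, using the specific gravity measured through a refractometer". The decision rule is: "A urine specific gravity cutoff of 1.25 will be applied". The action follows: "For higher values, the participants will drink 200–250 mL of water and wait 30 min before heat exposure". The section also includes "assessment of the urine color through the Armstrong urine color chart", but attaches no threshold or action to it. No other section gives a different specific gravity cutoff.

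Two other passages bear on safety in the heat arm:

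- **Stop rule** (Body temperature assessment and thermal sensation). The condition for ending a session begins "If a participant reaches a rectal temperature > 39.0°C and presents symptoms such as nausea" and goes on to list further symptoms.
- **Blood pressure.** The Interventions section reports from pilot work: "The HR increases and blood pressure, particularly diastolic pressure, decreases during the session". Safety and adverse events says: "Cardiovascular changes, such as increased heart rate and blood pressure, are expected and are not harmful".

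**The concern.** Specific gravity is density relative to water, so what matters is the excess over 1.00. A cutoff of 1.25 sets that excess at 0.25, far more than urine can reach. Because the drink-and-wait step is tied only to readings above the cutoff, a rule applied as printed clears every participant for entry, however concentrated the urine.

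The people concerned have type 2 diabetes and are about to spend 60 minutes in a chamber set at 55.0°C, three times a week for 12 weeks. The water preloading is self-administered on instruction. The specific gravity reading is the only pre-entry check on that preloading with an action attached, so if it cannot trigger, nothing in the written procedure detects a participant who did not drink.

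The stop rule is a separate and lesser matter. It joins temperature and symptoms with a conjunction. Read literally, a symptomatic participant below 39.0°C, or a participant above 39.0°C without symptoms, falls outside it. The text does not say that such a session must continue.

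**Working it through.** **Inputs from the article**

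- Cutoff 1.25, with action only above it (Hydration protocol).
- Heat-arm size: "the calculated total number of patients was 22 in each group" (Statistical considerations), with an assumed dropout of 10%.
- Three sessions a week (Interventions) for 12 weeks.
- HbA1c of 7.0% to 10% (Eligibility criteria), which makes urinary glucose relevant because it raises specific gravity.

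**Assumptions, not in the article**

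- Maximum urine specific gravity without glucose: 1.03 to 1.05.
- Effect of urinary glucose: about 0.004 per g/dL.
- Concentration: 25 to 40 mOsm/kg per 0.001 of specific gravity.
- Urine is tested before every session. The section reads that way but does not say so outright.

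**1. Excess over water.** At the cutoff: 1.25 − 1.00 = 0.25. Ratio to the largest attainable excess:

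| Assumed maximum | Largest excess | Ratio |
|---|---|---|
| 1.03 | 0.03 | 0.25 / 0.03 = 8.3 |
| 1.04 | 0.04 | 0.25 / 0.04 = 6.25 |
| 1.05 | 0.05 | 0.25 / 0.05 = 5.0 |

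**2. Urinary glucose.** Starting from 1.040 and adding an extreme 10 g/dL: 1.040 + 10 × 0.004 = 1.080, still far below 1.25. To reach 1.25 from 1.040 by glucose alone would take (1.25 − 1.040) / 0.004 = 52.5 g/dL.

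**3. Equivalent concentration.** An excess of 0.25 is 250 steps of 0.001. That is 250 × 25 = 6250 to 250 × 40 = 10000 mOsm/kg.

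**4. The likely intended value.** At 1.025 the excess is 0.025, and 0.025 / 0.25 = 0.1, one tenth of the printed excess. The equivalent is 25 × 25 = 625 to 25 × 40 = 1000 mOsm/kg. A reading above 1.025 is attainable under the assumed range, so the rule could then trigger.

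**5. Number of checks affected.** 3 × 12 = 36 sessions per participant, and 22 × 36 = 792 planned checks. If the 10% who drop out attended none, 792 × 0.9 = 713 (rounded). Checks that can exceed 1.25: 0 in either case.

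**Stop rule, by case**

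| Rectal temperature | Listed symptoms | Covered by the written rule |
|---|---|---|
| Above 39.0°C | Yes | Yes |
| Above 39.0°C | No | No |
| 39.0°C or below | Yes | No |

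**Blood pressure.** The pilot description reports a fall in the chamber. The safety section names only a rise and does not say in which arm. No stopping or recording action depends on that sentence.

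**The case against.** The strongest reply is that this is a misprint, not a decision. The purpose of the step is clear from its context, the same section also writes its per-kilogram water doses with a misplaced exponent, and a trained operator reading a refractometer would notice that 1.25 is impossible. Nothing in the article shows that staff apply 1.25. Other protections exist: preloading, continuous measurement of rectal temperature, heart rate and blood pressure during sessions, exclusion of people with cardiovascular disease, and supervision for at least 30 minutes afterwards. No outcome, sample size or analysis depends on the cutoff.

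Much of this stands. The figure probably is a misprint, and its effect in practice depends on what staff do, which the article cannot show. The remaining protections are real. But a misprinted threshold is still the written rule, the intended value appears nowhere in the article, and anyone who follows or replicates the protocol inherits it. Nor is this a detail left to a fuller document: the number is stated, and it is wrong.

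It is also fair to say that the count of 792 adds little, since the result is zero whatever the denominator, and that the number of preloaded participants who would exceed a correct cutoff is unknown. The practical safety effect is therefore not quantified.

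On the stop rule, the article does not call its condition exhaustive, and fuller criteria may sit in the full protocol. The pilot rise of about 1.2°C, from an assumed baseline of 37°C, gives about 38.2°C, so 39.0°C would not be typical. On blood pressure, the safety sentence may refer to exercise as well as heat, so it need not contradict the pilot finding. These are reasons to keep both points subordinate.

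**Conclusion.** The concern holds, with high confidence, and should be fixed. As printed, the specific gravity check cannot trigger at any of the planned chamber entries. The conclusion rests on an assumed range for human urine, but needs only that the maximum lie below 1.25. Even the extreme glucose case, at 1.080, uses less than a third of the excess required (0.08 / 0.25 = 0.32).

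The failure is confined to this one check. It does not mean that participants enter without protection, and it does not show that any participant entered under-hydrated. The joint condition in the stop rule is a secondary weakness of wording, and the blood pressure statement a minor one. The main conclusion depends on neither.

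**What to change.** - **Cutoff.** Replace 1.25 in the Hydration protocol with the intended value, probably 1.025, after confirming it against the cited method and the refractometer scale. Do this before any further heat sessions. Recruitment was planned to end in December 2025; if sessions are already complete, publish the correction all the same.
- **Past sessions.** Check the session forms for the figure that staff applied. If it was the intended one, only the text needs changing.
- **Stop rule (secondary).** Reword it so that either a rectal temperature above 39.0°C or the listed symptoms ends the session, subject to confirmation by the responsible clinicians. They should also decide whether a mild symptom such as tiredness is enough alone.
- **Blood pressure (minor).** State the expected change by arm in Safety and adverse events, consistent with the pilot description.

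The cost is one corrected figure and a note to session staff. Some sessions will start about 30 minutes later. An either/or stop rule may end a few sessions early and slightly reduce the heat dose delivered.

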### Safety and adverse events

Participants will be under continuous health professional control for at least 30 min after the intervention to prevent adverse events. The following mild and moderate adverse events can occur. Exercise protocols, particularly during maximum effort, can cause discomfort (nausea and muscle soreness). Heat therapy has been shown to be safe for most people.^
17
^ However, for some participants, it is possible that the higher temperature caused thermal discomfort. Cardiovascular changes, such as increased heart rate and blood pressure, are expected and are not harmful. Mild dehydration may be observed after completion of the protocol and will be attenuated by proper hydration.

## DISCUSSION

Inflammation markers are increased in individuals with diabetes.^
39
^ Strength training has been shown to be a highly efficient therapeutic practice in the prevention and treatment of diabetes,^
15,40
^as it is capable of manage systemic inflammation by decreasing CRP levels, with inconclusive evidence for other inflammatory biomarkers.^
41
^ Furthermore RT leads to subcutaneous abdominal adipose tissue reduction^
42
^ and improves HSR,^
14
^ which could improve T2DM control and prevent chronic complications.

The first study evaluating the effects of HT in diabetes was published by Hooper et al. in 1999, and its primarily resulted in glycemia, HbA1c and body weight decreases.^
43
^ Remarkably, there are few studies analyzing HT and its effects on diabetes metabolic control in humans, and the analyzed trials in a systematic review had methodological limitations that preclude the use of therapy in clinical practice, such as small sample size, observational study design, and short-term treatment.^
19
^ Recently, a cross-sectional study found that habitual hot-tub bathing was associated with slight improvements in HbA1c and body mass index.^
44
^In contrast, a randomized crossover trial showed that 90 min of hot water immersion did not improve insulin sensitivity, markers of micro- and macrovascular functions, or circulating and intracellular HSP70 concentrations.^
45
^ There is a lack of consistent data in the literature, and, furthermore, the possible mechanisms by which benefits can be obtained remain unknown.

Since the HSR response is decreased in individuals with diabetes,^
13
^ we believe that improving the HSR may be important in preventing chronic complications associated with T2DM. This randomized clinical trial will determine the efficacy of HT compared to RT in improving HR when combined with conventional therapy in individuals with T2DM. Multiple HT and RT effects may contribute to a lower mortality risk in these individuals. Our study is the first to evaluate the efficacy of HT and RT in glucose, lipid, and inflammatory profiles, microbiota, and HR measurements in individuals with T2DM. Moreover, we will maintain the experimental protocol for 12 weeks, which is the time necessary to obtain changes in the main parameter of diabetes control, HbA1c.

## CONCLUSION

Owing to its multiple effects, HT may prevent the comorbidities commonly associated with chronic hyperglycemia. The use of HT as an adjuvant treatment may improve the quality of life of individuals with T2DM, delay the onset of comorbidities, and reduce health costs, which are essential to prevent primary risk factors. This information will have immediate applicability in the promotion of public health.
